## Abstract

3DPN is a prospective, multicenter, randomized, controlled, two-armed open trial with planned recruitment of 370 patients in ten centers over a period of 24 mo. The trial is evaluating the value of virtual interactive 3D modeling for robot-assisted partial nephrectomy (RAPN) by assessing clinical outcomes, patient understanding, and surgeon confidence. Patients aged ≥18 yr with kidney tumors ≤7 cm who have contrast-enhanced computed tomography (CT) scans available and for whom RAPN with a da Vinci Surgical System is planned are eligible for the study. Using 1:1 randomization, patients are assigned to either the 3D model–based RAPN arm or the 2D CT scan–based RAPN arm.

This trial is registered on ClinicalTrials.gov as NCT06056505.

## Introduction and hypotheses

1

Renal cell carcinoma (RCC) ranks among the most common urological cancers along with prostate and bladder cancer, with more than 14 000 new cases annually in Germany in the past few years. Approximately 60% of RCCs are diagnosed at an early stage suitable for curative surgical treatment [1]. Recent developments in robot-assisted surgery have changed the distribution of surgical approaches between open, classic laparoscopic, and robot-assisted procedures in favor of robotic surgery. For instance, results from the British Association of Urological Surgeons demonstrated an increase in robot-assisted partial nephrectomy (RAPN) from 0% in 2008 to ∼62% in 2017, when RAPN exceeded the number of both open and laparoscopic partial nephrectomy (PN) surgeries [2]. However, given the anatomic structure of the kidney, tumors of similar size may vary highly in the level of difficulty for surgical resection, depending on factors such as proximity to the hilum or the calyceal system and endophytic versus exophytic growth. Different scoring systems have been proposed to classify renal tumors and standardize risk assessment. Ficarra et al [3] introduced the Preoperative Aspects and Dimensions Used for an Anatomical (PADUA) classification of renal tumors, and their prospective validation showed significant correlation between overall complication rates and the anatomic characteristics included in the score. The RENAL nephrometry score published by Kutikov and Uzzo [4] uses a comparable approach for reproducible quantitation of the complexity of renal lesions in the preoperative planning phase. In both classification systems, higher scores indicate more complex tumors, which increase the degree of surgical difficulty and thereby potentially impact the total operating time.

Current guidelines underscore the high significance of organ preservation in RCC surgery, with a strong recommendation for PN for T1 tumors [5]. The trifecta concept summarizes desired outcomes of PN, including negative surgical margins, maximal preservation of renal function, and complication-free patient recovery [6]. Preoperative surgical planning for each individual case is essential to achieve these goals. In current clinical practice, 2D computed tomography (CT) or magnetic resonance imaging scans are used to visualize anatomic relationships, and implementation of innovative 3D techniques is lacking. One such technique uses image segmentation from medical scans for virtual interactive 3D modeling [7]. These 3D models provide a patient-specific visualization of all crucial anatomical structures, including vessels, the renal collecting system, and the tumor, as well as their relative location to each other. This improves perception of the spatial relationships, which would otherwise require cognitive reconstruction of the different CT imaging planes [8]. This concept is supported by work by Amparore and colleagues [9], who recently showed that assessment of the complexity of renal masses with the PADUA and RENAL nephrometry scores was more accurate using 3D models.

With a virtual interactive 3D model, the surgeon can plan the operation in detail, for example, by identifying the location of vessels infiltrating the tumor, setting a strategy for exploration of the renal pedicle, and evaluating the proximity of the tumor to the pelvicalyceal system. Throughout the operation, the 3D model facilitates spatial orientation within the surgical field and makes it easier to define resection margins by clearly outlining the depth of tumor growth in comparison to a conventional CT scan. These potential improvements in surgical planning and strategy lead to the hypothesis that the process is more streamlined and results in a shorter operative time at the robotic console, and may eventually improve RAPN outcomes.

Since virtual interactive 3D modeling is a fairly new approach and surgical clinical trials are challenging to conduct, the data available—especially from large, randomized, multicenter studies—are limited. However, there is some evidence that 3D modeling may be a valuable tool to improve crucial parts of the surgical process [8,10]. For example, Shirk et al [11] reported shorter operating time, lower blood loss, and shorter clamp time and length of hospital stay for cases in which 3D virtual reality models were used during operative planning for RAPN. Furthermore, a recent case-matched study using 3D virtual models for minimally invasive PN demonstrated better outcomes with a lower reduction in estimated glomerular filtration rate (eGFR) and lower postoperative complication rates than in the matched group [12].

The aim of 3DPN is to investigate the utility of virtual interactive 3D modeling in RAPN by comparing this approach to conventional CT scans in a multicenter randomized controlled trial (RCT).

**Fig. 1 f0005:**
[figure not shown]
Study flow chart. CT = computed tomography; 2DPN = partial nephrectomy with 2D CT scans; 3DPN = partial nephrectomy with CT scans and 3D models.

**Fig. 2 f0010:**
[figure not shown]
The 3D modeling process.

Table 1 summarizes the data collection at four trial visits from baseline until follow-up 6 mo after surgery. Enrollment of the whole patient cohort is planned over a period of 24 mo. The trial opened in October 2023, with randomization of the first patient on October 24, 2023. After completion of follow-up, it is anticipated that results from the primary analysis of the trial will be available in the second quarter of 2026. The study is registered on ClinicalTrials.gov (NCT06056505).

**Table 1 t0005:** Schedule of assessments and procedures

Item		Visit 1 Baseline Enrollment and randomization	Visit 2 Surgery	Visit 3 Postoperative monitoring until discharge	Visit 4 Follow-up a 6 mo ± 8 wk after randomization
1	Inclusion and exclusion criteria	✓			
2	Patient informed consent	✓			
3	Randomization	✓			
4	Surgery consent b	✓			
5	Tumor characteristics	✓			
6	PADUA score	✓			
7	RENAL score	✓			
8	Oncological parameters c	✓		✓	
9	Comorbidities and medications (Charlson comorbidity index)	✓			
10	CT scan d	✓			
11	3D modeling e	✓			
12	Physical examination	✓			
13	Laboratory tests (blood count, creatinine, and eGFR)	✓		✓^f^	
14	Request for laboratory tests (creatinine and eGFR)				✓^g^
15	Urinalysis (albuminuria, hematuria)	✓			
15	Patient Reactions Assessment questionnaire h	✓			
16	Patient anxiety questionnaires (STOA, APAIS, NRS-A)	✓			
17	Patient satisfaction questionnaire	✓			
18	Surgeon confidence questionnaire		✓		
19	Adverse events		✓	✓	✓
20	Complications by Clavien Dindo grade		✓	✓	
21	Information on additional treatments				✓

APAIS = Amsterdam Preoperative Anxiety and Information Scale; CT = computed tomography; eGFR = estimated glomerular filtration rate; NRS-A = Numerical Rating Scale for Anxiety; STOA = State-Trait Operation Anxiety.

a Telephone interview with the patient by the study center in Leipzig (Department of Urology).

b With addition of a 3D model if the patient is randomized to the 3D model arm.

c May not be available until discharge.

d A contrast-enhanced CT scan of the patient’s kidney performed by an external physician is sufficient; the CT scan does not necessarily need to be performed at the study site.

e Only if the patient is randomized to the 3D model arm.

f According to local clinical routine, up to daily.

g Tests are requested via a fax form to the urologist in private practice, if available.

h All questionnaires are given to the patient after information on surgery is provided and consent is obtained, and before surgery is performed.

### Eligibility criteria

2.1

Patients are only considered eligible for the 3DPN trial if all the following inclusion criteria are met:•The patient has a kidney tumor ≤7 cm and RAPN with a da Vinci Surgical System is planned;•A contrast-enhanced CT scan is available;•The patient is aged ≥18 yr; and•The patient has provided written informed consent.

The following exclusion criteria apply at the time of eligibility evaluation:•History of surgery on the affected kidney (eg, PN, pyeloplasty, kidney cyst deroofing, percutaneous nephrolitholapaxy, radiofrequency ablation);•Clinical suspicion of metastases (stage cN1/cM1);•Horseshoe kidney;•Multifocal kidney tumor;•Von Hippel-Lindau syndrome and other hereditary kidney cancer syndromes;•Previous malignancy with ongoing or planned nephrotoxic chemotherapy;•Current immunosuppression (eg, organ transplantation, leukemia);•Tumor thrombus in the renal vein or inferior vena cava;•Severe cognitive impairment;•Pregnancy, lactation, or a woman who wishes to have children;•Patients under legal supervision or guardianship;•Inability to give informed consent or suspected lack of compliance; and•Patients who decline data collection and storage for the main study.

### Primary objective

2.2

The primary objective is to determine whether 3D modeling reduces the total console operation time for RAPN as a surrogate endpoint for PN outcomes such as perioperative complications and morbidity.

### Secondary objectives

2.3

Secondary endpoints include assessment of the patient benefit and aspects of treatment success and safety. These are categorized into three groups.

#### Preoperative

2.3.1

•Questionnaires are used to evaluate patient anxiety (State-Trait Operation Anxiety, Amsterdam Preoperative Anxiety and Information Scale, Numerical Rating Scale for Anxiety), patient comprehension of the surgical condition and the procedure planned (Patient Reaction Assessment), and patient satisfaction.

#### Intraoperative

2.3.2

•Hilar clamping technique (global ischemia, selective ischemia, clampless);•Warm ischemia time (WIT) in minutes;•Estimated blood loss;•Number of transfusions;•Total operative time measured from incision to suture in minutes;•Number of conversions to open surgery (reported intraoperatively);•Number of conversions to radical nephrectomy; and•Surgeon confidence level evaluated via a questionnaire survey (Supplementary material; study-specific questions on the impact of imaging on the following topics: spatial orientation, surgeon confidence during the procedure, surgical strategy, visualization of anatomical structures, satisfaction with the imaging available).

#### Postoperative

2.3.3

•Positive surgical margin rate;•Creatinine and eGFR according to the Chronic Kidney Disease (CKD)-Epidemiology Collaboration equation during the hospital stay and at follow-up at 6 mo ± 8 wk after randomization; and•Patient length of stay (recorded at discharge).

All secondary endpoints are exploratory, and no adjustment for multiplicity is foreseen. If the primary endpoint is not met, these objectives do not suffice to demonstrate the effectiveness of the tool, but may provide evidence suggesting its utility.

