### Complications and adverse events

2.4

The trial team assesses intraoperative complications and postoperative adverse events up to 6 mo after surgery and reports them as safety endpoints. The Clavien-Dindo classification scheme is used to grade postoperative complications.

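### The last follow-up contact is counted from randomization in two places and from surgery in two others, so adverse-event collection to 6 months after surgery is not guaranteed

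*Protocol article*

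**What the plan says.** Four places in the article date the end of follow-up.

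- **Table 1, column head for Visit 4:** "6 mo ± 8 wk after randomization". Footnote a makes this visit a telephone interview run by the lead center.
- **Section 2.3.3 (Postoperative):** creatinine and eGFR are assessed in hospital and "at follow-up at 6 mo ± 8 wk after randomization".
- **Section 2, sentence introducing Table 1:** data are collected at "four trial visits from baseline until follow-up 6 mo after surgery".
- **Section 2.4 (Complications and adverse events):** the trial team assesses "postoperative adverse events up to 6 mo after surgery and reports them as safety endpoints".

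Table 1 puts randomization at Visit 1 and surgery at Visit 2. Visit 3 ends at discharge, and Visit 4 is the only scheduled contact after that. The article gives neither a usual nor a maximum interval between randomization and surgery.

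**The concern.** The same contact is counted from randomization in two places and from surgery in two others, and nothing shown reconciles them. The two dates differ by the wait for surgery. That wait is not zero in the 3D arm at least, because the model is made only after allocation (Table 1, footnote e).

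Two things are at stake. Adverse events are a named safety endpoint with a stated period. After discharge, their scheduled collection depends on one telephone call. If that call comes before 6 months after surgery, reporting the events as collected over 6 months overstates the observation time for that patient. In addition, the follow-up creatinine and eGFR will be measured at differing times after the operation, so part of the spread between patients reflects timing.

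**Working it through.** **Inputs from the article.** Visit 4 is nominally 6 months after randomization, with a window of ± 8 weeks (Table 1, section 2.3.3). The adverse-event period is 6 months after surgery (section 2.4).

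**Assumed input.** The wait from randomization to surgery, *g* weeks, is not given. A range of 0 to 12 weeks is used here.

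**Conversion.** One month = 365.25/12 = 30.44 days. Six months = 182.6 days = 26.1 weeks. Eight weeks = 56 days.

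**The visit window as written.** Counted from randomization it runs from 182.6 − 56 = 126.6 days (4.2 months) to 182.6 + 56 = 238.6 days (7.8 months).

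**Time from surgery to Visit 4.**

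- Earliest = 182.6 − 56 − 7*g* days
- Nominal = 182.6 − 7*g* days
- Latest = 182.6 + 56 − 7*g* days

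| Assumed wait *g* | Earliest | Nominal | Latest |
|---|---|---|---|
| 0 weeks | 127 d (4.2 mo) | 183 d (6.0 mo) | 239 d (7.8 mo) |
| 2 weeks | 113 d (3.7 mo) | 169 d (5.5 mo) | 225 d (7.4 mo) |
| 4 weeks | 99 d (3.2 mo) | 155 d (5.1 mo) | 211 d (6.9 mo) |
| 8 weeks | 71 d (2.3 mo) | 127 d (4.2 mo) | 183 d (6.0 mo) |
| 12 weeks | 43 d (1.4 mo) | 99 d (3.2 mo) | 155 d (5.1 mo) |

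**Reading the table.**

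1. A call on the nominal date falls short of 6 months after surgery by exactly the wait.
2. With a wait of up to 8 weeks, a call late in the window still reaches 6 months after surgery. With a longer wait, no permitted call does.
3. The shortfall has two sources. With *g* = 4 the earliest call is at 26.1 − 8 − 4 = 14.1 weeks, which is 12 weeks short. Of these, 4 weeks come from the anchor and 8 from the early side of the window.
4. Re-anchoring to surgery with the same ± 8 weeks puts every call at 4.2 to 7.8 months after surgery, whatever the wait. This removes the dependence on *g*, but a call can still come before 6 months.

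**The case against.** The strongest reply is that this is loose wording in a condensed article, with little consequence. Several parts of it stand.

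- **The period can be reached.** A reader might infer that the 6-month postoperative period cannot be delivered at all. The table does not support that: with a wait of 8 weeks or less, permitted calls reach it. The section 2.4 period can also be read as an upper limit. What remains is that coverage is not assured.
- **The renal endpoint agrees with the schedule.** Section 2.3.3 and Table 1 use the same anchor. Only the general sentence above Table 1 suggests a postoperative date. Footnote g adds that these tests are requested by fax from the outpatient urologist, where there is one, so moving the call does not by itself fix laboratory timing.
- **Bias between arms is not shown.** A reader might infer that model preparation delays surgery in the 3D arm, shortens its observation and makes it look safer. The article does not say so. Table 1 lists modeling under Visit 1. Section 2.5 keeps patients whose model is missing at surgery in the 3D group and counts late models as a major violation. That reads more like surgery going ahead than being postponed. A different wait by arm remains possible, because only one arm needs a model from an outside company.
- **The reach is limited.** Clavien-Dindo grades are collected only at Visits 2 and 3. The safety set in section 2.5 holds only patients whose surgery was planned with a model. Secondary endpoints are exploratory, and console time does not depend on follow-up.
- **Randomization is a defensible anchor.** The full analysis set includes all randomized patients, and a patient who is not operated on has no date of surgery.

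Condensation does not remove the point. The article states both anchors, so this is a conflict between statements and not a detail left to the full protocol.

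**Conclusion.** The contradiction is real and should be resolved. If Table 1 is followed as written, adverse-event ascertainment to 6 months after surgery is not guaranteed. A permitted call can come at about 4.2 months after surgery with no wait, and at about 3.2 months (nominal 5.1) with an assumed 4-week wait. The 4.2-month figure rests only on the article's own window. All figures for a wait above zero rest on the assumed interval.

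Postoperative time at the follow-up creatinine and eGFR also varies between patients, through both the wait and the window. The documents do not establish a systematic difference between arms. The primary endpoint and the sample size are unaffected. The point concerns what is collected and how the safety and renal follow-up are described.

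**What to change.** 1. Reconcile section 2, Table 1, section 2.3.3 and section 2.4 to one anchor. The date of surgery is preferable for operated patients, with randomization kept for those not operated on.
2. Re-anchoring alone leaves the early side of the window open, so also do one of two things. Either state an adverse-event period that the permitted visit window can cover, or count events for all operated patients to a common postoperative day or by postoperative time at risk.
3. Analyse the follow-up creatinine and eGFR with days since surgery, taken from the date of the laboratory sample.
4. Report the randomization-to-surgery interval by arm. This shows whether the arms differ.

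**Cost.** An amendment to the wording and a recalculated call date. Either the call moves later by the wait for surgery, or the stated adverse-event period becomes shorter. The analysis steps need only the dates of surgery, call and sample. If these are recorded, the steps also work for patients already followed under the randomization-based window.

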### Complications and adverse events

2.4

The trial team assesses intraoperative complications and postoperative adverse events up to 6 mo after surgery and reports them as safety endpoints. The Clavien-Dindo classification scheme is used to grade postoperative complications.

### Statistical analysis

2.5

Existing data are limited as virtual interactive 3D modeling is a recent innovation. However, taking into account current results in the literature, we aim to show a reduction in mean operation time by 15 min, assuming this decrease is clinically (and economically) relevant. Furthermore, we propose a standard deviation for the operation time of 50 min. To detect the difference in operation time using a two-tailed Mann-Whitney *U* test, a sample size calculation via simulation using PASS 2008 software (NCSS LCC, Kaysville, UT, USA) resulted in 185 patients per group, assuming power of 80% and a significance level of 5%. No missing values are expected because the operation time can be assessed for every patient treated. We anticipate dropouts at later visits and will account for missing values for secondary endpoints using mixed models. To gain further insight into the data obtained, analyses will be conducted for three different study populations. (1) The full analysis set will include all randomized patients, with analysis according to their allocated trial arm; those for whom 3D models are missing by the time of surgery will remain in the 3D group. This set corresponds to the intention-to-treat principle in the International Council for Harmonization Good Clinical Practice guidelines. (2) The per-protocol set will consist of all patients undergoing RAPN without major protocol violations that affect the primary endpoint. Major violations include failure to acquire 3D models in time for surgery planning (excluded in this population). (3) The safety analysis set will include all patients for whom surgery was planned using a 3D model. Further analyses will include (mixed) linear models, logistic regression, and descriptive statistics.

### Data management and protection

2.6

Once patient eligibility is confirmed and informed consent to trial participation and data collection is obtained, the patient is assigned a unique patient identification code. Patient identification code lists are part of the investigator site file and remain at the recruiting site. These lists are the only documents that allow for reidentification of patients and can only be accessed by authorized members of the 3DPN study group. Clinical data are entered into electronic case report forms in a pseudoanonymized way using only the patient’s identification code. Data are collected at predefined time points, as summarized in Table 1.

The secuTrial database being used is protected against unauthorized access and validated according to standard operating procedures. The servers are physically located at Clinical Trial Center Leipzig (ZKS) in access-protected server rooms. All relevant trial documentation will be stored for 10 yrs after the end of the trial. After the archiving period, clinical data will be anonymized and stored for future use.

### Ethics and administration

2.7

The ethics committee of the primary study center in Leipzig (Ethik-Kommission der Medizinischen Fakultät Leipzig) granted ethical approval for the study (reference 185/23-ek), followed by all participating study centers. The first amendment of the trial was approved in January 2025 authorizing the current state of the protocol as outlined here.

### Trial supervision

2.8

ZKS is responsible for trial monitoring, including initiation, regular, and closeout visits at all trial sites. A risk-based monitoring strategy was implemented, as required by DIN ISO 14155 Chapter 6.7. During trial conduct, central and statistical monitoring procedures are combined with on-site monitoring visits to ensure high protocol compliance and data quality, and to guarantee patients’ rights and safety.

In addition, audits by an unbiased auditor are planned to guarantee trial compliance with DIN ISO 14155 and European and national laws.

## Discussion

3

Owing to the complexity of the renal anatomy, visualization of anatomic relations for PN can be challenging in terms of vascular supply and tumor localization despite multiplanar and thin-slice CT scans. The advent of innovative tools for 3D imaging in preoperative planning and intraoperative navigation holds the potential to improve these crucial steps. Piramide et al [10] summarized the existing evidence for 3D modeling in minimally invasive PN in a 2022 systematic review and meta-analysis. Among the nine RAPN studies included in the review, only the trial by Shirk and colleagues [11] was designed as an RCT and enrolled 92 patients. To date, the 3DPN study is the largest RCT in the field and is assessing the effects of virtual interactive 3D models on total console operation time, perioperative and postoperative outcomes, psychological parameters at the patient level, and surgeon confidence.

The choice of the primary endpoint was based on the literature on RAPN. For example, Kim et al [13] showed a ∼20% reduction in console operation time in comparison to the matched control group, while there was no significant difference in WIT. Furthermore, 3D modeling might particularly be helpful for renal hilum preparation and tumor localization, neither of which would be reflected by WIT. Achieving a shorter operation time would automatically lead to a shorter anesthesia time, which is associated with a lower risk of complications [14]. Previous studies revealed a higher complication rate for longer operation times, especially for thromboembolism [15] and infections [16,17] in both general and urological surgeries. In the PN setting, a recent matched case-control study showed that after adjustment for covariates, virtual 3D modeling reduced the estimated average operation time from 201 min to 143 min [18].

Another advantage of 3D reconstruction is the potential to avoid radical nephrectomy in some cases. In an exploratory study of PN cases in which 3D modeling was retrospectively added to conventional CT diagnostics, indications for PN increased by 27% after surgeons reviewed the 3D model in addition to the CT scan [19]. Higher rates of organ preservation reduce the number of patients with CKD or other chronic conditions, with a consequent reduction in the number of hospital visits. The 3-yr probability of freedom from new-onset CKD was 35% after radical nephrectomy versus 80% after PN [20]. In addition, patients undergoing PN had a lower incidence of cardiovascular events in comparison to RN [21]. These factors can lead to higher quality of life and longer life expectancy with PN while maintaining oncologic control.

At the patient level, 3D modeling could facilitate patient understanding and improve overall satisfaction [22]. The SPLICE prospective RCT investigated an informed consent process involving 3D virtual reality for patients undergoing intracranial tumor resection. The results revealed higher objective comprehension of their condition for patients in the 3D group, while subjective comprehension and anxiety levels did not differ significantly between the study groups [23]. The 3DPN trial aims to investigate corresponding effects in the specific setting of PN.

Recent literature also supports the benefits of 3D reconstruction for surgeons. Better visualization of anatomical structures can lead to more informed decision-making about the operative approach, and modification of the surgical strategy after reviewing the 3D model in some cases [24,25]. Exploratory analyses will focus on the impact of visualization and surgeon confidence during PN.

As the 3DPN study follows standard-of-care treatment for renal tumors up to 7 cm and adds 3D images as a supplementary tool to standard CT imaging, no added risk is anticipated in the interventional arm. Furthermore, scans that are already available are used to render the 3D model, and no further invasive tests or added exposure to radiation are necessary.

Despite its strengths, the study has a few limitations. For instance, the endpoints being investigated could be influenced by the level of surgeon experience. To limit this performance bias, participating surgeons need to demonstrate a minimum of 100 previous robotic kidney surgeries. Moreover, patient stratification is based on BMI and the PADUA classification of renal tumors as a surrogate for tumor complexity. Unfortunately, not all renal lesions fit the schema of the anatomical criteria included, and scores can underestimate or overestimate the risk.

In summary, our goal is to demonstrate the utility of virtual interactive 3D modeling in a multicenter randomized clinical trial in ten high-volume tertiary care hospitals in Germany that perform PN regularly. We want to generate strong clinical evidence that could guide current PN practice in Germany and worldwide.

  ***Conflicts of interest***: The authors have nothing to disclose.

  ***Funding support****:* This study is funded by Deutsche Krebshilfe (German Cancer Aid; grant number 70114653).
